
## Methods and Analysis

### Participants and Study Design

This is a prospective cohort study made up of four groups with a specific diagnosis (stroke, spinal cord injury, knee OA, or lower limb amputation) and a group of healthy volunteers.

Patients admitted to the conventional rehabilitation program of the Instituto de Medicina Física e Reabilitação (IMREA) will be invited to participate in the study and included after signing the informed consent form previously approved by the Hospital das Clínicas da Faculdade de Medicina da Universidade de São Paulo Ethics Committee for Research Protocol Analysis CAAE: 86832518.7.0000.0068. For this study, 400 patients will be recruited, 100 patients with a stroke diagnosis, 100 with knee OA, 100 with spinal cord injury, and 100 amputee patients. The control group will be made up of 100 healthy subjects paired by sex and age.

Patients who agree to participate in the study will undergo a series of assessments at two time points: before and after the IMREA rehabilitation program. An individualized approach characterizes this program, considering the injury's etiology, the type of disabilities the patient has, general clinical conditions, likely prognosis, and the patient's socioeconomic factors. The control group will only perform neurophysiological (EEG, fNIRS, and TMS) and functional assessments once.

It is important to note that all patients involved in the research will receive the same type of treatment as patients who are not participating in the research.

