### Clinical and Functional Assessments

At the beginning of the study, on the participant's first visit, a trained physician will take the patient's history, perform a physical examination, and review the eligibility criteria for that patient. The obtained information from the patient's history such as age, sex, height, weight, ethnicity, education level, medications in current use, comorbidities, and the specific characteristics of each injury will be used as covariates in the final linear regression model.

Several instruments that allow the global assessment of participants, general or specific to each condition, were selected (Table 1 and Appendix 1). Some scales, such as cognitive, sleep, and mood scales, will be used to characterize the study's sample, as well as for the management of confounding variables on the multivariate statistical model.

**Table 1 T1:** Assessment instruments used for each study group.

**Category**	**Instrument**	**Amp**.	**Stroke**	**OA**	**SCI**	**CG^*^**
Independence	Functional Independence Measure (FIM) (11)	X	X	X	X	X
Independence (Specific to SCI)	Spinal Cord Injury Independence Measure (SCIM III) (12)				X	
Cognition	Montreal Cognitive Assessment (MOCA) (13)	X	X	X	X	X
Cognition (speach)	Semantic verbal fluency test (14)		X			
Pain	Conditioned Pain Modulation (CPM) (15)	X	X	X	X	X
Pain	Pressure Pain Threshold (PPT) (16)	X	X	X	X	X
Pain/Sensitivity	Monofilament Sensitivity Test (17)	X	X	X	X	X
Pain/Sensitivity	Tuning Fork Vibration Sensitivity Test (18)	X	X	X	X	X
Pain	Pain Catastrophizing Scale (19, 20)	X	X	X	X	
Pain	McGill Pain Questionnaire (Brazilian Version) (21)	X	X	X	X	
Pain	Visual Analogue Scale (VAS) for Pain (22)	X	X	X	X	
Lower Limb Motor Function	6-min and 10 meters gait test (23)	X	X	X	X	X
Lower Limb Motor Function	Timed Up and Go (TUG) (24)	X	X	X	X	X
Lower Limb Motor Function	Lower Limb Isokinetic Dynamometer (25)	X	X	X	X	X
Lower Limb Motor Function	Walk Index for Spinal Cord Injury (WISCI-II) (26)				X	
Upper Limb Motor Function	Fugl–Meyer Assessment (FMA) (27)		X		X	
Upper Limb Motor Function	Hand Grip and Pinching (28–30)		X		X	X
Upper Limb Motor Function	Purdue Pegboard Test (PPBT) (31)		X		X	X
Upper Limb Motor Function	Robot-Measured Kinematic Variables (32)		X		X	X
Upper Limb Motor Function	Finger Tapping (FT) (33)		X		X	X
Upper and Lower Limb Motor Function	Medical Research Council Scale (MRC) (34)		X	X	X	
Balance	Force platform (35)	X	X	X	X	X
Balance	Berg Balance Scale (36)	X	X	X	X	

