In the statistical analysis for the results of the obtained polymorphisms, classical methods of case–control studies' epidemiological analysis will be applied. Odds ratio and the respective 95% confidence intervals will be estimated by unconditional logistic regression to simultaneously control potential confounding variables. To assess the relationship between the dependent variable (stroke and its subtypes) and the independent variables (polymorphisms of the evaluated genes, smoking, lipid variables, etc.), the statistical technique used will be logistic regression analysis, which allows the evaluation of disease risk associated with a given variable considering all other independent variables in the model.

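### The genotype odds ratio for stroke is to be read conditional on lipid variables, which cannot confound a germline genotype and have no stated pre-stroke time point

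*Protocol article*

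**What the plan says.** All points are from the protocol article.

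- **Statistical Analysis, last paragraph.** The polymorphism results are to be analysed by case-control methods. Odds ratios with 95% confidence intervals are "estimated by unconditional logistic regression to simultaneously control potential confounding variables". The outcome is "the dependent variable (stroke and its subtypes"), and the predictors are "the independent variables (polymorphisms of the evaluated genes, smoking, lipid variables, etc".). The model is said to be one that "allows the evaluation of disease risk associated with a given variable considering all other independent variables in the model". The genotype odds ratio is therefore conditional on lipids and smoking by the text's own reading.
- **Participants and Study Design.** Cases are "Patients admitted to the conventional rehabilitation program", so they enter after the stroke. "The control group will be made up of 100 healthy subjects paired by sex and age".
- **Clinical and Functional Assessments.** The history covers "age, sex, height, weight, ethnicity, education level, medications in current use, comorbidities, and the specific characteristics of each injury", and these items are assigned to the linear model. Smoking and lipids are named neither there nor in Table 1. Table 1 lists genotyping for all five groups; the genes are not named.
- **Statistical Analysis, second paragraph.** Ethnicity is among the characteristics to be tested in the motor-improvement regression.

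**The concern.** A confounder of genotype and stroke must be a cause of genotype or share a cause with it. Germline genotype is fixed at conception, so a lipid level cannot be its cause. Ancestry is the usual common cause of genotype frequency and disease risk.

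The lipid value may also lie downstream of both genotype and case status. A patient admitted to rehabilitation has had the stroke and probably treatment for it, and no earlier lipid measurement is specified. For a variant that affects lipids, conditioning on such a value links genotype to stroke even when no link exists. If the lipid value does predate the stroke and lies on the path from gene to stroke, conditioning on it removes the effect being sought. In neither case does the adjustment help to estimate the total genotype effect.

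At stake is whether a reported polymorphism finding, positive or negative, reflects the gene or the adjustment.

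**Working it through.** **Inputs.** The article gives no odds ratio, allele frequency or power for the genotype model, so there is no figure of its own to reproduce. Its sample-size statement concerns the linear regression. From the documents: 100 stroke patients and 100 controls. Every other input below is an assumption.

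**1. Lipids measured after the stroke, no genotype effect on stroke.** Let *G* be the allele count, *D* = 1 for a case, and lipid *L* = *g·G* − *d·D* + *e*, with *e* standard normal. Here *g* is the shift per allele and *d* the lowering by stroke or its treatment, both in SD. The log likelihood ratio for *D* given *L* and *G* is

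−½(*L* − *gG* + *d*)² + ½(*L* − *gG*)² = −*dL* + *gd·G* − *d*²/2.

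The lipid-adjusted genotype odds ratio is therefore exp(*g·d*), although the true value is 1. Simulations used 100 v 100, allele frequency 0.3 and 600 data sets per setting; ranges cover repeated runs.

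| *g* | *d* | exp(*gd*) | Simulated OR | False positives at 5% |
|---|---|---|---|---|
| 0.2 | 0.5 | 1.11 | 1.12 | 6–8% |
| 0.3 | 1.0 | 1.35 | 1.36 | 21–24% |
| 0.4 | 1.5 | 1.82 | 1.89 | 55–59% |
| either is 0 | | 1.00 | about 1.00 | 4–5% |

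Without lipids in the model the rate is about 5% throughout. The Monte Carlo standard error near 55% is √(0.55 × 0.45/600) = 2 percentage points. A repeat with 3,000 data sets gave 7%, 22% and 55% for the first three rows. With carrier coding, shifts of 0.3 and 0.5 SD give exp(0.15) = 1.16, and 0.5 and 1 SD give exp(0.5) = 1.65; large simulated fits agree.

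**2. Lipids measured before the stroke, as a pure mediator.** Suppose carriers are 0.5 SD higher, the log odds of stroke rise by 0.5 per SD, and the gene acts only through lipids. The total odds ratio is about exp(0.5 × 0.5) = 1.28 (1.27 in a large simulated case-control set). After lipid adjustment it is 1.00.

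**3. Smoking.** With genotype unrelated to smoking, and half of the smokers among cases having quit, the genotype odds ratio stays at 1.01 with or without the adjustment.

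**4. Ancestry left out, no genotype effect within ancestry groups.** With a share *s* from group A and carrier frequencies *a* and *b* in the two groups, the carrier frequency is *s·a* + (1 − *s*)*b*.

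- Shares 40% (cases) v 30% (controls), *a* = 0.3, *b* = 0.2: 0.24 v 0.23, OR (0.24/0.76)/(0.23/0.77) = 1.06.
- Shares 60% v 30%, *a* = 0.5, *b* = 0.1: 0.34 v 0.22, OR (0.34/0.66)/(0.22/0.78) = 1.83.
- Equal shares: OR 1.00.

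In a simulation with allele frequencies 0.2 and 0.5 and shares 50% v 30%, false positives were 20–24% without ethnicity in the model and about 5% with it.

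**5. Scale.** With carrier frequency 0.3 and 100 v 100, the standard error of the log odds ratio is √(2/30 + 2/70) = 0.309. The 95% interval is the estimate times or divided by exp(1.96 × 0.309) = 1.83, and the smallest odds ratio detectable with 80% power is exp(2.80 × 0.309), about 2.4. Most of the biases above are smaller than this sampling error, but they act in one direction.

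**The case against.** The strongest reply is that the paragraph describes a multi-risk-factor model in a condensed article. Smoking and lipids can be read as risk factors of interest in their own right, the list is open-ended, and the full covariate list may stand elsewhere. The genes are not named, so nothing shows that any of them acts on lipids. No source or time point for lipids is given, so values from pre-stroke records cannot be ruled out. All magnitudes rest on assumed inputs, and the low end of the range is close to nominal.

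Much of this stands, and it rules out several stronger readings:

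- A reader might infer that lipids and smoking are consequences of genotype or of stroke. The documents do not establish either.
- A reader might infer that one of these paths is enough. It is not: the bias is the product *g·d*, which is zero if either path is absent.
- A reader might infer that smoking adjustment does damage. None is shown, unless genotype affects smoking.
- A reader might infer that ethnicity is excluded. It is collected and named for the motor model, and the wording here, which ends openly and speaks of potential confounders in general, leaves room for it.

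What the reply does not answer is the lipid choice. It is written into the text, not omitted from it, and the text says that the genotype coefficient is to be read given lipids. That reading has no confounding-control benefit to set against its risks.

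**Conclusion.** The point holds in a limited form. Conditioning the genotype odds ratio on lipids is a stated choice with three possible results:

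- It creates an association if the variant affects lipids and stroke or its treatment shifts them: odds ratio about 1.1 to 1.9 and false-positive rate about 6 to 56%, for 0.2 to 0.4 SD per allele and 0.5 to 1.5 SD between cases and controls.
- It hides a real effect if lipids are a pre-stroke mediator (1.27 to 1.00 in the example).
- It is neutral if the variant does not affect lipids.

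Which result applies cannot be told from the article, because it gives neither the genes nor the timing of the lipid measurements.

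The ancestry point is secondary. Pairing covers sex and age only, and ethnicity is not named for this model, but the bias is zero if patients and controls have the same ethnic mix.

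The matter is minor. It concerns a subsidiary analysis, and a reader should not carry it over to the motor-improvement regression or the sample size, which do not depend on it.

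**What to change.** In the last paragraph of Statistical Analysis, make two changes:

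1. State that the main genotype odds ratio for stroke is adjusted for age, sex and ethnicity, without lipids.
2. Present the model that adds smoking and lipids as a secondary risk-factor model. Give the time point and source of both variables, and say that this model is not used to interpret the polymorphisms.

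The cost is a sentence or two. Age, sex and ethnicity are already collected, so no new data are needed. The downside is that ethnicity, if self-reported, captures ancestry only partly, so some residual confounding would remain and should be acknowledged when results are reported.

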## Discussion

This study will help understand the relationship between the brain plasticity biomarkers and functional disability not related to a specific etiology but related to central and peripheral neural injury. In addition, we expect that this study is going to build a better understanding of the brain modification associated with prosthesis adaptation and movement adaptation assisted technologies in patients with stroke and spinal cord injury. We also expect that we are going to be able to understand better the relationship between these biomarkers and motor deficit and other functional disabilities. Thus, the current challenge is to identify in human beings how multiple aspects of brain plasticity that happens in an integrated way influence the process of rehabilitation and to understand how different types of lesions in the peripheral and central nervous system modify the balance of brain plasticity.

We chose these four different conditions (stroke, spinal cord injury, OA, and amputation), as in all of them, we can find patients passing through maladaptive neuroplasticity regarding pain and disability (56–60). This approach may allow us to explore the possible transdiagnosis markers linked with plasticity in disability and pain regardless of the diagnosis label usually touched by the literature. One of the justifications that aim to explore these biomarkers is that chronic pain and disability conditions may share similar maladaptive changes regarding neuronal plasticity (61, 62).

In this study, we are looking to test and explore the neural inhibition through TMS, EEG, fNIRS, and MRI that have an impact on the rehabilitation clinical practice. We will also classify biomarkers as follows: (i) substitute, which indicates the biomarkers are modified with the “successful” rehabilitation; (ii) prognosis, which indicates the biomarkers indicate functional recovery regardless of rehabilitation therapy; and (iii) predictive, which indicates the biomarkers predict treatment response. We will investigate the activity of theta, delta, and beta waves on EEG, rMT, EMP, SICI, ICF, CS, and SP on TMS, the brain metabolic activity on fNIRS, and the motor cortex's volumetric mass on MRI to assess these aspects as potential biomarkers, characterizing them as either substitute, prognostic, or predictive (63).

The development of (i) substitute results for functional recovery and the understanding of the factors that influence the rehabilitation process will be possible to develop consistent and feasible studies. Currently, the majority of the studies in this field have low statistical power, without control of confounding variables, and reproducibility problems (64). In addition, the lack of substitute markers has allowed the approval of therapies without the background of consistent methodological studies. These distortions are not harmless and overwhelm the health system.

Another biomarker that we expect to identify is (ii) prognostic. The current models to determine the functional prognosis of patients with stroke or spinal cord injury are not accurate, making the therapeutic approach difficult. These biomarkers could specify the patient's recovery potential, providing earlier hospital discharges and avoiding unnecessary treatments. One example is a pain biomarker in spinal cord injury using intracortical inhibition. Studies have shown that subjects with spinal cord injury and pain have decreased intracortical inhibition (65, 66).

The final biomarker that we aim to identify is (iii) predictive of functional recovery. In this case, we are going to identify the plastic brain modifications that are related to functional recovery and that are induced by rehabilitation therapy (67). This understanding will allow the individualization of the treatment and potentialize future insights about the new approaches of rehabilitation.

To our knowledge, there is a lack of studies designed to understand brain plasticity in the rehabilitation context, and there is too little knowledge in the mechanisms involved in the balance between neural inhibition and excitability and in brain plasticity regulation. Also, the current literature has had a low impact on the rehabilitation practice.

In this context, TMS is a widely used tool to measure corticomotor excitability in patients with motor deficit conditions such as stroke. It has been found that motor deficit severity is highly associated with the level of corticomotor excitability measured by rMT depicted in TMS results. Given that rMT reflects neuronal membrane excitability, functional modifications that occur after motor deficit conditions, such as inhibitory circuit malfunctions, are reflected as rMT alterations in TMS (68). We expect to find a reduction in inhibitory brain activity associated with a decrease in rMT, SICI, and SP due to the direct relationship between these biomarkers and motor inhibitory pathways of the brain. Moreover, study findings show that ICF and MEP are mediated by different interneuronal pathways than those of rMT, SICI, and SP; thus, it is expected that as inhibitory circuits increase their activities, ICF and MEP amplitudes will be decreased (69).

Several studies have conveyed brain plasticity alterations in the primary motor cortex. These changes have been thus identified through the use of biomarkers such as EEG and fNIRS, for instance, strong correlations between theta and delta band activities in the hippocampus and successful inhibitory mechanisms in rodent models (70). The use of EEG as a biomarker “tracker” thus becomes important because sensory inhibition reflects an automatic cortical inhibition function, which can be used as a measure of the brain's inhibitory status (71–74). These findings support one of the study's main hypotheses that motor function deficits are associated with lower cerebral inhibitory activity when compared with a healthy control group. Studies that have performed electrophysiological evaluations of patients with chronic pain conditions such as OA, spinal cord injury, and neurogenic pain have found a decrease in theta and delta wave activity and an increase in beta wave activity due to deficient brain inhibitory circuits (75). Thus, an increase in the activity of theta and delta bands, as well as a decrease in beta bands, is a reflection of increased inhibitory activity, which can be achieved through rehabilitation in patients with pain conditions. Therefore, given these findings, we expect a diminished event-related desynchronization in patients with motor dysfunctions.

The association of EEG and fNIRS have been used in many studies to analyze cortical activation and plasticity connections in the context of rehabilitation (76). Both tools are practical, non-invasive methods of measuring brain activity; however, fNIRS lacks good spatial and temporal resolution and cannot assess deep brain structures (75). Thus, its association with EEG provides a more holistic understanding of cortical activation in the conditions being studied. Moreover, it has been shown that electrophysiological variations have the ability to predict hemodynamic activation in motor regions of the brain (77).

Different studies have found an inverse relationship between fNIRS results and efficient inhibitory networks, given that efficient inhibitory networks depict less cortical activation in prefrontal regions during executive function tasks. Therefore, we hypothesize that, as patients undergo rehabilitation, their inhibitory networks will be strengthened, which will then be depicted on the fNIRS as a decrease in activity, bolstering the use of fNIRS as a tool for plasticity biomarker measurement (78). However, evidence on this relationship is still conflicting. For instance, a study evaluating the feasibility of fNIRS as an assessment mechanism for patients with spinal cord injury has conveyed enhanced activation of motor cortical areas after rehabilitation with robot-assisted gait training (78). Given that fNIRS produces blood-oxygen-level-dependent images, this suggests a link between the brain's metabolic activity in the motor cortex and recovery of gait-impairing conditions such as SCI and stroke, which is still unclear. Thus, the use of fNIRS to evaluate neuroplasticity biomarkers in this study will help to further elucidate the relationship between neuroplasticity and brain hemodynamic activity.

Moreover, the use of more conventional imaging methods, such as MRI to evaluate the transdiagnostic nature of plasticity biomarkers, has become very promising given the association between cortical thickness and chronic pain (79, 80), amputations (81, 82), spinal cord injury (83, 84), and stroke (85, 86). These correlations support the analysis of volumetric measurements of the motor cortex to yield a better understanding of this relationship.

This is a novel and feasible observational study that will help the understanding, improvement, and development of the rehabilitation field and allows for the identification of several biomarkers at once, providing further insight for clinical practice in rehabilitation. Furthermore, this study was designed to answer our hypothesis in an optimized way, with a rigorous methodology. Besides that, one of the limitations is that our results will not provide a causal relationship between neurophysiological markers and functional and clinical outcomes. Also, the study may be underpowered, as there are four groups of intervention; to minimize that, we performed a sample size calculation based on the expected effect size regarding previous studies; the neurophysiological surrogate variables are something that could help to address this limitation also. The differences between severities of conditions could lead to different dropout rates in one of the more severe group conditions; this may unbalance the groups' size. Another limitation is that the variability of the clinical phenotypes of the conditions approached by this study could generate some noise in our results. To minimize this limitation, we are planning to do a multivariate analysis, which could minimize relevant confounders that may interfere with our results. Finally, our study may lack generalizability, as the study will be performed in only one center.

On the other hand, this is a novel and feasible observational study that, as mentioned before, will help the understanding, improvement, and development of the rehabilitation field.

In conclusion, understanding brain plasticity in the context of rehabilitation allows for more effective approaches and provides screening evaluations of current rehabilitation techniques. The future results of this study will help to better understand brain plasticity and its mechanisms and its reliable representative biomarkers as well. This knowledge will lead to the development of rehabilitation as has occurred in other fields, such as cardiology. In this context, simple questions such as the posology of the treatment will start to be answered when we have markers to measure the functional recovery and feasible and powered studies will be able to be performed in an extensive and consistent manner.

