### Statistical Analysis

For this analysis, we will use the multivariate regression model in which motor improvement will be the dependent variable and changes in inhibitory activity (resulting from neurophysiological assessments performed before and after treatment) will be the independent variables.

To control the impact of different conditions on the multivariate model, we will create a “dummy variable” for each disease etiology. Moreover, demographic characteristics (age, education, sex, and ethnicity) and clinically relevant characteristics (duration of illness, comorbidities, and the use of medications) will be tested, as well as specific aspects for each disease, such as the stroke side, the level of spinal cord injury, the degree of bone deformity of knee OA, and the level of lower limb amputation. The neurophysiological biomarkers described earlier will be tested in the same model.

Although this study's aim is not to test interventions but to identify changes in biomarkers related to functional improvement (regardless of the therapy performed), the different therapies performed by patients will be quantified, including information such as the number of sessions, frequency, duration, among others, which can be used in future analyses.

For secondary analyzes, functional improvement can be assessed by the several, general and specific, scales used depending on the evaluated disease. In this situation, we will use the calculation of the functional modification's effect size and not the absolute values of the scale for the analysis in the multivariate model.

Also, the motor function of the upper limb will only be assessed for patients with stroke and spinal cord injury, the main scale used being the Fugl–Meyer Assessment. In this case, an analysis similar to the one described earlier will be performed but only including these two populations.

Some of the scales, such as those for mood, pain, cognition, and sleep, will be used to characterize the sample, in addition to possibly being used to control confounders in the multivariate model. Besides, mood, pain, and cognitive disorder are commonly present in these populations, so we will perform an exploratory analysis using a similar statistic method but with scales related to these aspects as dependent variables.

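### The plan promises to label markers substitute, prognostic or predictive, but its stated recovery model addresses at most the substitute class, and with every patient rehabilitated the design cannot separate prognostic from predictive markers

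*Protocol article*

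**What the plan says.** **Classes promised (Discussion).** The article undertakes to classify the markers and lists EEG bands, TMS measures, fNIRS activity and motor cortex MRI as candidates. A substitute marker is one modified when rehabilitation succeeds. The second class is "prognosis, which indicates the biomarkers indicate functional recovery regardless of rehabilitation therapy". The third is "iii) predictive, which indicates the biomarkers predict treatment response".

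**Second meaning of predictive (Discussion, later paragraph on that class).** Here the text says "we are going to identify the plastic brain modifications that are related to functional recovery and that are induced by rehabilitation therapy".

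**Model (Statistical Analysis).** The outcome of the main regression is motor improvement. On the predictor side, "changes in inhibitory activity (resulting from neurophysiological assessments performed before and after treatment) will be the independent variables". Etiology dummies and covariates are added. It continues: "The neurophysiological biomarkers described earlier will be tested in the same model". The secondary, upper-limb and exploratory analyses reuse this structure with other outcomes or populations. Therapy sessions, frequency and duration are recorded, but only for possible future analyses.

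**Design (Participants and Study Design).** Patients are recruited from those admitted to the rehabilitation program and assessed before and after it; "all patients involved in the research will receive the same type of treatment as patients who are not participating in the research". The program is individualized, with likely prognosis among the factors considered. Controls are healthy and assessed once.

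**Limitation (Discussion).** The article concedes that its results will not establish causal relationships between markers and outcomes.

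**The concern.** A marker that forecasts recovery has to be known before recovery is observed. A pre-to-post change is known only at the final visit, when motor improvement is known too, so its association with improvement is concurrent.

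Telling recovery regardless of therapy apart from response to therapy also needs patients who differ in whether they were treated. Here none goes without rehabilitation, and the healthy controls have neither a disability to recover from nor a second assessment.

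At stake is the label put on a result. If the classification is carried out on the stated model, concurrent correlates could be reported as prognostic or predictive. The Discussion attaches practical hopes to those labels, among them individualized treatment.

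**Working it through.** **The plan's own figure.** The only numerical target is 100 patients per group, 10 covariates and an effect size of about 0.3 (Sample Size). Alpha, power and the effect-size metric are not stated. If 0.3 is a correlation, tested at two-sided 5%, the Fisher z formula gives 85 patients for 80% power and 113 for 90%, or 94 and 122 with nine other covariates. So 100 is plausible but cannot be uniquely reproduced. The present point does not depend on it.

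**Step 1: what can be estimated when everyone is treated.** Let B be the baseline marker, T treatment (1 = rehabilitated) and Y motor improvement:

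E(Y) = a + b1·B + b2·T + b3·B·T

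A purely prognostic marker has b1 ≠ 0 and b3 = 0. A predictive marker has b3 ≠ 0. With T = 1 for every patient this becomes

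E(Y) = (a + b2) + (b1 + b3)·B

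The design matrix [1, B, T, B·T] has rank 2 of 4. Only b1 + b3 is estimable: b1 = 0.3 with b3 = 0, and b1 = 0 with b3 = 0.3, both give a slope of 0.3. Controls cannot supply rows with T = 0, because they have no Y.

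**Step 2: what the change-only model detects.** Assumed inputs: n = 400 treated patients, baseline B and change dB independent with unit variance, residual SD 1, true coefficient 0.3, two-sided 5% tests, 4000 runs.

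| Truth | Change-only model rejects | Coefficient on B when B is added |
|---|---|---|
| Purely prognostic | 4.9% | 0.300 |
| Purely predictive | 5.0% | 0.299 |
| Purely substitute | 100% | about 0 |

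The change-only model finds baseline effects at no more than the false-positive rate. Adding B detects both baseline types in 100% of runs but cannot tell them apart.

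Independence of B and dB is an assumption. If their correlation is ρ, the change-only slope under either baseline truth is 0.3ρ. For ρ = −0.3 that is 0.3 × (−0.3) = −0.09. The model then picks up the baseline effect indirectly, with the sign reversed, and still cannot separate the classes.

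**Step 3: the two meanings of predictive, side by side.**

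- First meaning: the marker forecasts response, so it is a property held before therapy.
- Second meaning: the marker is a brain change that therapy causes and that goes with recovery, so it is observed after therapy. This nearly repeats the substitute class.

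Attributing the change to therapy requires the change that would have occurred without it, which no patient supplies. It also sits badly with the article's own non-causal limitation.

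**Step 4: whether a baseline-marker model is feasible.** Assumptions, none stated in the article: 14 model terms, two-sided 5%, 80% power, one marker tested (noncentral F). The smallest detectable partial correlation is about 0.14 with all 400 patients and about 0.16 with 320 (20% loss: 400 × 0.8). MRI is analysed in 10% of patients, or 40. With the same 14 terms the detectable value there is about 0.42 to 0.50, depending on the noncentrality convention.

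**The case against.** Several stronger readings are tempting, and the document does not support them.

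- **That prognosis cannot be studied here at all.** It can. Baseline markers and later outcomes are both collected, so prognosis among rehabilitated patients is estimable. Out of reach is only the article's own qualifier, that the marker holds regardless of rehabilitation.
- **That baseline levels are excluded.** The sentence putting the other biomarkers in the same model does not say level or change, and the EEG and MRI sections do not say so either. A fuller analysis plan may include a baseline term. This is fair, but no later plan can create an unrehabilitated comparison or reconcile the two meanings of predictive.
- **That the change-on-change model is wrong for substitute markers.** It fits that class as the article defines it. Only a stricter notion of surrogacy, which the article does not adopt, would fault it.
- **That treatment does not vary.** Intensity does vary and is recorded. But the program is shaped partly by likely prognosis, so a marker-by-dose analysis would be confounded by indication.
- **That the study would itself justify "providing earlier hospital discharges and avoiding unnecessary treatments".** The article says only that such markers could help in this way, which is a hope for the field and not a decision rule of this study.

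It is also fair that the three-way classification appears only in the Discussion. The aim in Statistical Analysis, to find marker changes related to improvement, matches the planned model. Even so, the classification is worded as something the study will do.

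**Conclusion.** The point holds in this limited form. Of the three promised classes, the stated recovery model can address at most one. Of the other two, prognosis can be recovered in a narrower sense from data already collected, while prediction of treatment response, as distinct from prognosis, cannot be identified in this design.

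The rank result rests only on every patient being rehabilitated and on the controls having no recovery outcome, both of which follow from the article. The rejection rates rest on the simulation assumptions, and the detectable correlations on an assumed number of terms, power and loss. The feasibility figures show that the remedy is workable for most markers; they do not measure the defect.

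The two meanings of predictive contradict each other whatever model is used. The main association analysis and the data collection are unaffected.

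**What to change.** 1. Prespecify a second model: post-program motor score on baseline marker, baseline motor score, etiology and covariates. Report positive findings as prognostic among patients receiving rehabilitation. Limit MRI markers to the 40-patient subset and state its lower precision.
2. Drop the predictive claim or label it hypothesis-generating. Any baseline marker by therapy-dose analysis should be exploratory, with the caveat that therapy is individualized partly by likely prognosis.
3. Use one definition of predictive throughout the Discussion, and remove wording that attributes marker changes to therapy.
4. Keep the change-on-change model for the substitute class as the article defines it, reported as association only.

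The cost is one extra regression on data already being collected, and narrower claims in the text. No new patients or assessments are needed.
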